**INTRODUCTION**

The study presented below is part of a doctoral thesis, which consists of four differentiated and longitudinal parts over time. Each of the parts is related to one of the objectives set out in the thesis

| Objectives | Type of study |
| --- | --- |
| 1. Develop a graded motor imagery (GMI) protocol for a patient with phantom limb pain (PLP) after an amputation. | Systematic review |
| 1. Validate the developed protocol. | Study with Delphi methodology |
| 1. Analyze the effectiveness of the protocol in this patient profile. | Randomized clinical trial |
| 1. Know the experience of living with PLP and identify the satisfaction obtained with the intervention. | Phenomenological study |

The first part of the thesis consisted of a systematic review. Its purpose was to analyze the effectiveness of the GMI and each of the techniques that make it up (lateral recognition, motor imagery and mirror therapy) in the amputee patient. This review made it possible to analyze the details of the intervention used (intensity, frequency, duration) in each of the techniques in order to later elaborate the protocol. Once the protocol was designed, the second part of the thesis consisted of its validation. A group of national and international experts in the field of neurorehabilitation and / or pain validated the protocol through a study with Delphi methodology. This second study validated the GMI protocol called the GraMI protocol. These first two parts of the thesis were passed by the ethics committee of the University of Vic-Universitat Central de Catalunya (UVic-UCC) on January 25, 2021 with a favorable opinion with code 143/2021.

We are currently in the third part of the thesis, which aims to conduct a randomized clinical trial (RCT) to analyze the effectiveness of the GraMI protocol on phantom limb pain, quality of life, functionality and associated psychological aspects. In parallel with the RCT, it is also intended to carry out the fourth part of the thesis, which will consist of a phenomenological study in order to know the experience of living with PLP and identify the satisfaction obtained with the intervention. These last parts have also passed the ethics committee of the University of Vic-Universitat Central de Catalunya on November 22, 2021 with a favorable opinion with the code 185/2021.

Below are all the aspects related to these last two studies.

1. **BACKGROUND:**

The International Association for the Study of Pain defines phantom limb pain (PLP) as that pain or sensation referred to in a part of the body that has been previously removed as if it were still present(1,2). It affects between 55-80% of the population who has suffered an amputation, but not in the same way, frequency and intensity, therefore, there is no single definition of PLP as each person perceives it differently(3). In most cases, it appears the week after the amputation, but it can also appear after a few weeks or even months. In many cases it can last for years and become a chronic pain(4). There are different theories that try to explain the neurological basis of phantom limb pain, but there is no one dominant theory over the others. It is known that after amputation there is an alteration that causes changes at the peripheral, spinal cord and central level and can be associated with psychological disorders, such as depression or anxiety, which can influence the chronicity of the pain and the quality of life of the person (1,5,6). The main hypothesis is that after amputation, maladaptive plasticity occurs in the primary motor and sensory cortex, causing an incongruity of information between visual, motor and sensory, responding to pain. Currently, there are different lines of treatment to try to lower PLP; pharmacological, surgical and physiotherapeutic therapy(3).

GMI is a form of physiotherapeutic treatment, progressive, designed to train and reorganizes the brain based on three consecutive and progressive techniques: restoration of laterality, motor imagery and mirror therapy(6). GMI is based on different neuroscientific foundations, such as neuroplasticity and the use of mirror neurons with the idea that the reorganization of the cerebral cortex could help reduce pain(5).

1. **JUSTIFICATION:**

There is scientific evidence of GMI in the field of chronic pain, especially in the area of ​​complex regional pain syndrome, which shows positive effects in reducing pain(7,8). However, little evidence is found on the implementation of GMI in the patient with PLP after amputation(9). As a result, there is a need to design and validate an GMI protocol to address the PLP and test its effectiveness. The aim of this protocol is to provide healthcare professionals with a standardization of the intervention.

For all this, at the beginning of the thesis a systematic review was carried out in order to know the effectiveness of the GMI, and the techniques that form it, on the PLP in the amputated patient, and thus, to be able to design a protocol. of IMG based on scientific evidence. The systematic review, carried out between December 2020 and January 2021, revealed the effectiveness of the three techniques that make up the GMI in the PLP, but in those studies where the combination of the three techniques was used together, it was more effective. This protocol was subsequently validated by a group of international experts through a study with the Delphi methodology, resulting in the GMI protocol called GraMI. This Delphi study was published in the journal IJERPH on November 30, 2021(10).

The GraMI protocol allows the patient to perform it autonomously and individually at home with the follow-up of a professional. It is necessary to have a mirror box and a mobile application to be able to carry out the intervention. Today, the majority of the population has access to new technologies, which generate more motivation, dynamism, adherence and continuity with the intervention compared to other techniques(8).

1. **HYPOTHESIS**

The GraMI protocol can have a positive effect on the decrease in PLP in the amputee patient, and as a result, it can decrease the associated psychological factors and improve the person's quality of life and functionality.

1. **OBJECTIVES**

**Main objective:**

- To study the effectiveness of the GraMI protocol on PLP in the amputee patient.

**Specific objectives:**

- Design a mobile application to be able to carry out the intervention and determine its usability.

- Analyze the effectiveness of the GraMI protocol in the quality of life, functionality and psychological aspects of amputated patients.

- Know the experience of the person with PLP after amputation and identify the satisfaction obtained with the intervention

1. **DESIGN**:

A RCT with a mixed methodology will be carried out, with two parallel arms and blindly simple, following the recommendations of *the Consolidate Standards of Reporting Trials - CONSORT*(11), and a phenomenological study through semi-structured interviews, following the recommendations of *the Standards for Reporting Qualitative Research*(7) which will be carried out once the intervention is over. The clinical trial was registered at ClinicalTrials.gorv (registration number: NCT05083611).

1. **SETTING:**

It will be done at the community level individually. The intervention will be carried out by the participant himself / herself and will be supervised with a follow-up by the principal researcher. The semi-structured interviews will be individual and carried out in person or by video call once the intervention is over.

1. **SIMPLE SIZE**

The sample was calculated using the G * Power program, taking into account an alpha error of 0.5, a beta error of 0.8, and an effect size of 0.81(9). In order to calculate the sample we rely on existing scientific evidence. A study11 has been selected to assess phantom limb pain using the McGill Pain Short-Form Questionnaire, and the intervention used is based on mirror neurons. The total number of participants would be 50, with 25 in each group.

1. **INCLUSION AND EXCLUSION CRITERIA:**

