The data obtained as study variables will be coded at the end of the collection, processed and analyzed by the members of the research group.

The population to be used as a sample in the analysis will include all participants who meet all the inclusion criteria, do not have any exclusion criteria and have given their consent to participate in the study. If a participant leaves before completing the study, he / she will not be replaced by another participant.

In the case of participants who have not completed the study due to dropout, have not fully completed treatment, or have even changed treatment, any data that may have been collected will be analyzed for intent to treat. The minimum number of sessions to be considered for the results will be 80%.

The program to be used for statistical analysis will be the SPSS5 program. A confidence level of 95%, and / or a statistical significance p <0.05 will be considered.

If a deviation from the intended method is considered necessary during the data analysis process, the reasons for any change will be fully documented.

To describe the sample, a descriptive statistic will be performed analyzing the mean, standard deviation, minimum, maximum and percentages of the sociodemographic variables. In addition, it will be possible to look at the average of those included and excluded in order to justify the excluded people. In this way it will be possible to describe the sample and observe the homogeneity between groups.

Next, a univariate and bivariate statistical analysis will be performed. First of all, it will be assessed whether or not the study follows a normal distribution in each of the variables. This analysis will determine whether to use parametric or non-parametric tests in the analysis of results based on the "p" value.

Equality of variance will then be analyzed through the Levenne test and finally the results will be analyzed. There will be a pre- and post-intervention analysis between groups and intragroups with a three-month follow-up. We can also analyze possible correlations between variables.

Qualitative analysis:

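### The sample-size statement misreports its error rates: alpha 0.5 and beta 0.8 do not give 50 participants, and alpha 0.5 contradicts the 0.05 test level in the analysis section

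*Protocol*

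**What the plan says.** The sample-size section (headed Simple size) of the protocol names G*Power as the software and gives these inputs: "taking into account an alpha error of 0.5, a beta error of 0.8, and an effect size of 0.81(9". It concludes: "The total number of participants would be 50, with 25 in each group". The design section describes a trial "with two parallel arms and blindly simple". The test, its sidedness and any dropout allowance are not stated.

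The quantitative part of the statistical analysis section sets a 95% confidence level and says that "a statistical significance p <0.05 will be considered". It adds that participants who leave are not replaced.

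On the source of the effect size, the figure itself carries reference 9 ("an effect size of 0.81(9"). Two sentences later the same paragraph says "A study11 has been selected to assess phantom limb pain". In the reference list, entry 9 is, by its title, a study of short-term virtual-reality neurorehabilitation for phantom limb pain. Entry 11 is the CONSORT 2010 explanation paper.

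**The concern.** Alpha, power and effect size are the whole justification for the number of participants. Two of the three are printed with values that cannot be what was used. An alpha of 0.5 conflicts with the protocol's own significance rule. A reader who takes "a beta error of 0.8" at its word concludes that the trial has a one-in-five chance of detecting the effect it was sized for.

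What is at stake is whether an ethics committee, a journal or a later reader can check the size of the trial from the text. The test level applied to the results is set in the analysis section and is not affected.

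**Working it through.** **Inputs.** From the sample-size section: effect size 0.81, alpha 0.5, beta 0.8, 25 per group, two equal groups. From the analysis section: alpha 0.05 with 95% confidence. Assumed, because the protocol names neither: 0.81 is a standardised mean difference (Cohen's d), and the test is the independent-samples t-test.

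**Method.** With n per group, the test statistic follows a noncentral t distribution with 2n − 2 degrees of freedom and noncentrality d × √(n/2). Power is the probability that it exceeds the critical value. The required n is the smallest whole number, at least 2, that reaches the target power.

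**Reproducing the stated 50.** Take two-sided alpha 0.05, power 0.80 and d = 0.81.

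- Normal approximation: n = 2 × (1.960 + 0.842)² / 0.81² = 2 × 7.851 / 0.6561 = 23.9, so 24 per group.
- Noncentral t: n = 24.92, so 25 per group and 50 in total. At n = 25 there are 48 degrees of freedom and the noncentrality is 0.81 × √12.5 = 2.864. Power is 0.784 at 24 per group and 0.801 at 25.

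**Keeping one or both printed values** (noncentral t, d = 0.81):

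| Alpha | Power | Two-sided: per group / total | One-sided: per group / total |
| --- | --- | --- | --- |
| 0.5 | 0.2 (both as printed) | 2 / 4 | 2 / 4 |
| 0.5 | 0.8 (0.8 read as power) | 7 / 14 | 3 / 6 |
| 0.05 | 0.2 (beta as printed) | 5 / 10 | 3 / 6 |
| 0.05 | 0.8 (both corrected) | 25 / 50 | 20 / 40 |

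In the first row, 2 per group is simply the smallest size for which the t-test exists; it already has power 0.61 two-sided and 0.79 one-sided. Seen from the other end, alpha 0.5 with 25 per group has two-sided power 0.986.

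**Dropout.** Inflating the largest of the first three rows for 20% loss gives 14 / 0.8 = 17.5, so 18. That does not approach 50. In the last row, the one-sided total inflated for 20% loss gives 40 / 0.8 = 50. So 50 has two possible derivations, and both need alpha 0.05 and power 0.80.

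**The case against.** The strongest reply is that this is a misplaced decimal point and a mislabelled quantity, and that the 50 is easily recovered from conventional inputs. That stands, and it limits the point. Several stronger readings are tempting but not supported:

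- **A reader might infer that the trial accepts a 50% false-positive rate and an 80% chance of missing the effect.** It does not. Inference is governed by the 95% confidence level and p < 0.05 in the analysis section, and 25 per group has about 80% power at that level under the assumptions above.
- **A reader might infer that a two-sided t-test must have been used.** It is the natural reading: it gives 50 directly, and a 95% confidence level suggests two sides. It is not proven, because one-sided alpha 0.05 with a 20% dropout allowance also gives 50. The protocol mentions neither a one-sided test nor such an allowance.
- **A reader might infer that the effect size cannot be traced.** The figure itself carries reference 9, a phantom-limb-pain study. The unbracketed 11 looks like a leftover from older numbering. The protocol has other unbracketed numbers that do not fit the list, such as a reference 26 for the intervention-reporting guide when the list ends at 18. The two citations still disagree and need reconciling.
- **A reader might infer that 0.81 is the wrong kind of effect, for instance a pre-post change.** The protocol does not say which kind it is, and the source is not available here, so no error can be shown.

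The reply does not remove the discrepancy. The printed values are wrong, and nothing elsewhere in the protocol corrects them.

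**Conclusion.** The point holds as a reporting error in the stated error rates. Alpha is printed ten times too large (0.5 against 0.05), and 0.8, which fits only as power, is labelled as beta, whose matching value is 0.20. As printed, the inputs imply 4 participants in total; correcting only one of the two gives at most 14; correcting both gives 50.

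The sample size, the operative test level and the conduct of the trial are unaffected. The conclusion that the printed values cannot give 50 assumes that 0.81 is Cohen's d and that two independent means are compared by a t-test; under those assumptions it holds for one-sided and two-sided tests, and with up to 20% dropout inflation. The match to exactly 50 without inflation also assumes a two-sided test. On that reading the 50 contains no dropout allowance, so any loss takes power below 0.80.

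**What to change.** In the sample-size section, change alpha to 0.05 and describe 0.8 as power (beta 0.20). Add the test and its sidedness as they stand in the saved G*Power output, and say whether any dropout allowance was included. If that output shows the two-sided independent-samples t-test, the sentence would give two-sided alpha 0.05, power 0.80, standardised effect size 0.81, and 25 per group, 50 in total. The authors should confirm this rather than adopt it by inference.

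In the same paragraph, cite one source for the 0.81. Reference 9 fits by its title and entry 11 cannot be the source study, but the authors must confirm which was used, and should state what kind of effect the 0.81 is.

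The cost is one corrected sentence and one citation, with no change to design, enrolment or analysis.

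### The 25 per group is the bare minimum of complete outcomes for 80% power, with no stated allowance for the dropout that the protocol foresees and will not replace

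*Protocol*

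**What the plan says.** The Protocol's section headed Simple Size (sample size) names G*Power as the software and gives the inputs as "taking into account an alpha error of 0.5, a beta error of 0.8, and an effect size of 0.81(9"), where the 9 is a literature citation. The result is "The total number of participants would be 50, with 25 in each group". The section does not name the test or the number of tails, and it does not mention loss to follow-up. The Design section describes two parallel arms.

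The Statistical Analysis section, under Quantitative analysis, sets the significance level: "A confidence level of 95%, and / or a statistical significance p <0.05 will be considered". It then says "If a participant leaves before completing the study, he / she will not be replaced by another participant". For people who drop out, do not finish treatment or change treatment, it plans an intention-to-treat analysis of whatever data were collected. It also sets 80% as the minimum share of sessions for the results.

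The Removal list under the eligibility criteria adds two grounds: a change in medication that affects pain, and a change in prosthesis use. Outcomes are assessed at baseline, at 9 weeks and again 12 weeks later. No expected dropout rate appears anywhere in the document.

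**The concern.** The enrolment target and the no-replacement rule are both fixed in the protocol, and they do not fit together. If 25 per group is the smallest number that reaches 80% power, it must be the number analysed, not the number enrolled. A protocol that provides for leavers and rules out replacing them should either enrol more or state a lower power.

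What is at stake is how a non-significant result is read. A reader who takes the trial as 80% powered for an effect of 0.81 SD would give a null result more weight than it deserves if several outcomes are missing. At 21 weeks from start to last assessment, with a home programme in one arm, some loss is plausible.

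**Working it through.** **Inputs.**
- Effect size d = 0.81, SD = 1, 1:1 allocation, 25 per group: sample-size section.
- Alpha = 0.05: Statistical Analysis section. The sample-size section prints 0.5.
- Power = 0.80: my reading of the phrase "a beta error of 0.8".
- Two-sided two-sample t-test: assumed, as neither test nor tails is stated.
- Loss rates: assumed, 5% to 20%.

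**Formula.** With n1 and n2 complete outcomes, df = n1 + n2 − 2 and the noncentrality is δ = d·√(n1·n2/(n1+n2)). Power is the probability that a noncentral t with these parameters falls outside ± the 0.975 quantile of the central t.

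**Step 1: reproduce the plan's figure.** For 25 and 25, δ = 0.81 × √12.5 = 2.864, df = 48, critical value 2.011, power 80.1%. Solving for 80% gives n = 24.92, rounded up to 25. The printed values taken literally (alpha 0.5, with 0.8 as power) give 7 per group two-sided or 3 one-sided, so they cannot be the values used. The 25 is reproduced, and the reserve is only the rounding from 24.92.

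**Step 2: one outcome missing.** 25 against 24 gives 79.3%; 24 against 24 gives 78.4%.

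**Step 3: equal loss in both arms, unadjusted test.**

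| Assumed loss | Complete per arm | Power | Effect detectable with 80% power (SD) |
|---|---|---|---|
| 0% | 25 | 80.1% | 0.81 |
| 5% | 23.75 | 78.0% | 0.83 |
| 10% | 22.5 | 75.7% | 0.86 |
| 12% | 22 | 74.7% | 0.87 |
| 20% | 20 | 70.4% | 0.91 |

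Fractional numbers are averages.

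**Step 4: loss in the intervention arm only.** The home programme has 30 + 30 + 15 = 75 sessions (two a day for 15 days in each of the first two phases, one a day for 15 days in the third). It applies to one arm; controls continue usual treatment with a diary. 25 against 22 gives 77.4%, and 25 against 20 gives 75.2%.

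**Step 5: adjustment for baseline.** If r is the correlation between baseline and outcome score, the residual SD is √(1−r²), so the effective size is 0.81/√(1−r²): 0.849 at r = 0.3 and 0.935 at r = 0.5. (The one degree of freedom spent on the covariate is ignored.)

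| Complete per arm | r = 0.3 | r = 0.5 |
|---|---|---|
| 25 | 84% | 90% |
| 22 | 79% | 86% |
| 20 | 74% | 82% |

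The correlations are assumptions; the protocol gives none.

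**The case against.** **The 25 may already contain an allowance.** The hypothesis is directional and the tails are unstated. A one-sided t-test needs 19.56, so 20 per group, and 20/0.8 = 25. On that reading 20 complete outcomes per arm still give 80.8%. This cannot be excluded, but the document states neither a one-sided test nor a 20% allowance, while the two-sided calculation reaches 25 directly. It remains a reason to ask for test and tails to be stated.

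**Intention to treat keeps people in.** This stands in part. Someone who misses sessions or changes treatment can still be assessed and analysed. The 80% session rule, which can only apply to the intervention arm, counts as loss only if it overrides the intention-to-treat statement. The same goes for removals that are still assessed. How these rules fit together is a separate question about the analysis set. Analysing collected data does not, however, supply outcomes that were never collected.

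**No loss rate is given, so the shortfall is speculative.** Its size is. A reader might infer that real power will be around 65% to 75%, or that the evaluable number is certain to fall below 25 per arm. The document supports neither. That power range needs roughly 12% to 28% loss in both arms, and the dropout wording is conditional. At 5% to 10% loss the shortfall is 2 to 4 points.

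**A separate statistical analysis plan could specify an adjusted analysis.** It could, and that may restore the power. The protocol describes only normality checks, a test of equal variances, and parametric or non-parametric comparisons between and within groups.

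**Conclusion.** The point holds as an omission in planning, not as a miscalculation: 25 per group is correctly derived under the likeliest reading of the inputs. It is the number needed with complete outcomes, and the protocol treats it as the number to enrol while foreseeing unreplaced dropout. Under the unadjusted two-sided t-test, any missing outcome takes power below 80%.

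The size depends on assumed loss: about 78% at 5%, 76% at 10% and 70% at 20% in both arms, and 75% if the intervention arm alone falls to 20. The conclusion rests on reading the printed alpha and beta as 0.05 and power 0.80, and on two-sided testing. It weakens the interpretation of a null result and does not invalidate the trial.

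**What to change.** Keep 50 participants and change the sample-size section as follows.

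1. Correct the printed error rates to those actually used (apparently alpha 0.05, and beta 0.20, that is power 0.80), and name the test and the number of tails.
2. State that 25 per group gives 80% power for d = 0.81 only with complete data, and give the power and detectable effect at a stated loss rate. For example, 20% loss in both arms leaves about 70% power, or 80% power for 0.91 SD, with an unadjusted test.
3. In the Statistical Analysis section, make the between-group comparison of the short-form McGill score adjusted for its baseline value, which is already collected. State the assumed correlation and the resulting power: with 20 per arm, about 74% at r = 0.3 and 82% at r = 0.5.

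The cost is a few sentences, with no extra participants or assessments. The stated power becomes less favourable unless the adjusted analysis is adopted and the correlation is high enough. If 25 complete outcomes per arm are to be kept under the unadjusted test, the alternative is to enrol 25/(1 − loss) per arm: 28 at 10% loss or 32 at 20%, that is 56 or 64 in all.
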